##### Dynamic postural stability

To develop the study, the NeuroCom Balance Manager System (Version 9.3, Copyright ©1989–2016 Natus Medical Incorporated) will be recruited to determine postural stability by measuring the participants’ centre of gravity (COG) alignment at a sampling frequency of 100 Hz. The balance platform is equipped with 18×60″ dual-force plate to measure the vertical forces exerted through the participant’s feet. We will conduct the sensory organisation test (SOT) and limits of stability test (LOS) to evaluate the static postural stability. Similarly, the participants will be informed of all procedures in advance. They will be positioned with standardised foot placement relative to individual height and be instructed to stand facing forward, with their arms relaxed at their sides and to remain as still as possible. The participants will remove all footwear and be restricted by a seat belt.

For the SOT, the participants will perform all balance trials and repeat each trial three times [32]. The movements of COP will be recorded with the participants standing under six conditions (as shown in Table 1). The duration of running each condition was 20 s. In all trials, the assessor will not alert the participants to impending changes of surrounding or the platform, but the assessor will only instruct them to open or close their eyes. Each participant will complete these six trials in the random order.

**Table 1 Tab1:** Six conditions in sensory organisation testing

Test condition	Eyes	Surroundings	Platform
1	Open	Fixed	Fixed
2	Closed	Fixed	Fixed
3	Open	Sway referenced	Fixed
4	Open	Fixed	Sway referenced
5	Closed	Fixed	Sway referenced
6	Open	Sway referenced	Sway referenced

By the combination of vision, surrounding and contact surface, the SOT test creates sensory-conflict situations and helps to evaluate the capacity to maintain postural stability under these sensory conflicts. According to the sway and sway velocity of COP, the system will generate equilibrium scores of each condition. An overall composite equilibrium score will be calculated using a weighted average of these scores and be used for analysis. A high equilibrium score means a low postural sway, indicating greater postural stability [33].

Furthermore, the LOS test will be conducted to measure the maximum distance by which a participant can intentionally displace COG [34]. The same standing position will be instructed as in the SOT test. In a different step, the computer screen at eye level in front of the participant will be turned on, depicting a centre box with eight target boxes equally spaced in an elliptical arrangement around the centre (as shown in Fig. 2). Participants will be instructed to shift their weight so that an icon (the projection of their COP) is held steady in the centre box. After the tone, they will lean their body to move the icon in these eight directions without losing balance, lifting their feet, or reaching for assistance. They will hold the icon steady in the target box until the second tone and return to the centre box. The test will begin with the target in a forward position and move in a clockwise direction.

**Fig. 2 Fig2:**
[figure not shown]
Limits of stability test

The performance for trials in each of the eight directions will be recorded and used to calculate the following indicators. First is directional control, or the amount of movement in the intended direction minus the amount of extraneous movement, expressed as a percentage. Second is end-point excursion, or the distance travelled by the COG on the primary attempt to reach a target, expressed in percentage. Third is maximal excursion, or the furthest distance travelled by the COG. Fourth is movement velocity (average speed of the COG shift towards the target, measured in degrees per second).

The outcome data of dynamic postural stability (SOT and LOS tests) will be formatted as the scores at the points of baseline (week 0), post-intervention (week 12) and follow-up (week 24). The values will be shown as mean and standard deviation.

##### Self-reported postural stability

The Berg Balance Scale will be used to evaluate the postural stability of individuals in daily activities, which is widely used in scientific research for the elderly or patients with balance dysfunction [35]. It includes 14 questions scored from 0 to 4. The participants will rate according to the degree of difficulty. The outcome of Berg scale will be recorded at the points of baseline (week 0), post-intervention (week 12) and follow-up (week 24). The scores of Berg scale will be shown as proportion.

##### Self-reported number of falls

In addition, the number of falls in the last 3 months will be recorded by each participant. According to 12-week period of intervention and follow-up, the participants will be asked to recall the falls in the last three months in order to determine the treatment effect of these intervention. Similarly, the number of falls will be reported by participants at the points of baseline (week 0), post-intervention (week 12) and follow-up (week 24). The scores of berg scale will be shown as proportion.

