##### Intrinsic-foot-muscle exercise combined the lower extremity resistance training group (IFM)

Participants in the IFM group will be instructed to perform short-foot exercise according to the methods used in a previous study [25]. Under the supervision of the physical therapist, they will shorten their feet in the anterior-posterior direction without curling the toes, by actively drawing the head of the first metatarsal towards the heel. In short-foot exercise, the foot should be held for 5 s per repetition. The intensity of exercise will be divided into three levels (sitting position, double-leg stance and single-leg stance) with the overload increasing progressively. In general, for weeks 1–4, the IFM will be performed in a sitting position, subsequently performed in double-leg standing for weeks 5–8, and finally performed in single-leg standing for weeks 9–12.

Meanwhile, participants in the IFM group will undertake lower extremity resistance training. Thera-Band® resistance bands (The Hygenic Corporation, Akron. OH, USA) will be used during strength training. Likewise, training sessions will be supervised by a physical therapist to ensure correct training method and provide security. The programme of lower extremity resistance training includes extended leg raises, hip abduction, hip adduction, hip extension, knee extension, knee flexion, ankle plantarflexion and ankle dorsiflexion. The training will be progressed by increasing the strength of resistance bands to provide greater resistance.

The exercise regimen will comprise 3 blocks of 12 repetitions for IFM and resistance training, with a 2-min rest period between blocks. Each set will be performed bilaterally. Three sets will be performed 3 times per week for 12 weeks.

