##### Control group

The participants in the control group will perform the same lower extremity resistance training as the IFM and EFM groups. The training will also be supervised by the physical therapist. The entire intervention will be conducted under the protocol of the IFM and EFM groups and for the same duration.

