#### Follow-up after intervention

The three groups will follow their respective training programmes for 12 weeks and will be followed up for another 12 weeks. After the intervention period, the participants will undergo a 12-week training period at home. During follow-up, they will be asked to maintain their previous lifestyle and continue interventions, respectively, and the physical therapist will provide guidance by telephone approximately once every 2 weeks. At week 24, these participants will return the laboratory and be reassessed.

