#### Adverse event reporting and harms {22}

The interventions that involve strength training will be performed under the supervision of the qualified physical therapist. Even during the follow-up period, the guidance will be provided weekly for the security of home-based interventions. All participants will be instructed to report any abnormal reactions or uncomfortable feelings experienced to any researcher. Additionally, all adverse events will be recorded truthfully in the trial. The physical therapist and outcome assessors will also collect and record adverse events or any other unintended effects during the interventions and laboratory test, such as musculoskeletal problems (i.e. muscle strain or joint pain). These results will be reported to the main investigator in weekly research meetings.

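### Falls are taken only from three-month recall at weeks 0, 12 and 24, although existing sessions and calls would allow dated recording in every arm

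*Protocol article*

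**What the plan says.** In the protocol article, the section Self-reported number of falls, listed under secondary outcomes, states that "the number of falls in the last 3 months will be recorded by each participant". It adds that participants will be "asked to recall the falls in the last three months", and gives the purpose: "in order to determine the treatment effect of these intervention". The same recall is taken at weeks 0, 12 and 24. The article describes no diary, calendar or log kept between visits.

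Contact with participants is otherwise frequent:

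- **Weeks 1 to 12.** For the IFM group, "Three sets will be performed 3 times per week for 12 weeks". The EFM section gives the same frequency. The control section sets the same duration and states: "The training will also be supervised by the physical therapist".
- **Weeks 13 to 24.** Under Follow-up after intervention, "the physical therapist will provide guidance by telephone approximately once every 2 weeks". The retention section {18b} and the adverse-event section {22} both say weekly instead.
- **Throughout.** Section {22} says "all adverse events will be recorded truthfully in the trial". It does not name falls.

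**The concern.** The choice of instrument is stated, so this is not detail that the article leaves to a fuller document. It asks people over 60 to remember about three months of events, in a trial that sees or calls them far more often. Each forgotten fall is lost information on an outcome with few events.

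A smaller point concerns the window. Visits are 12 weeks apart, but three calendar months are slightly longer. Taken literally, the week-12 count reaches back before week 0, and the week-24 count reaches back into the intervention period. A fall near a visit could then be counted at two of the three time points that the statistical section treats as distinct.

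**Working it through.** The plan gives no expected fall count and no power figure for falls. Its one computed figure, 98 participants, reproduces with an effect size of 0.25 in a repeated-measures MANOVA interaction test (3 groups, 3 times, power 0.8005), but falls play no part in it.

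**Inputs from the document.** 40 participants per arm, 120 in total (Sample size); visits 12 weeks, or 84 days, apart (Outcomes); a three-month recall window (Self-reported number of falls); one fall in the 6 months before entry (Inclusion criteria).

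**Assumptions.** The entry rate of one fall per 6 months (182 days) continues; 10% to 30% of falls are forgotten; counts are Poisson; fall rates before week 0 are equal across arms; the week-12 visit is 84 days after randomisation.

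**1. Available contacts**
- Weeks 1 to 12: 3 × 12 = 36 sessions, so recall shortens from about three months to 2 or 3 days.
- Weeks 13 to 24: 12 / 2 = 6 calls or 12 calls, depending on which section applies, so recall shortens to 14 or 7 days.

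**2. Loss of falls through forgetting**
- Expected true falls in 12 weeks: 120 × 84/182 = 55.4, or 18.5 per arm.
- Reported if 10% are forgotten: 55.4 × 0.90 = 49.9.
- Reported if 30% are forgotten: 55.4 × 0.70 = 38.8, or 12.9 per arm.
- Standard error of a two-arm log rate ratio with all falls: √(2/18.5) = 0.329.
- After 30% loss: √(2/12.9) = 0.394, a ratio of 0.394/0.329 = 1.20.
- In general the ratio is 1/√(1 − p) for forgotten share p, so it does not depend on the assumed fall rate. It is 1.05 at 10% and 1.20 at 30%. If falls cluster within people, the relative increase is smaller.
- If both arms forget the same share p, the observed ratio is (1 − p)λ₁ / (1 − p)λ₀ = λ₁/λ₀. Equal forgetting therefore costs precision and leaves the rate ratio unchanged.

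**3. Window, read literally**
- Three calendar months are 89 to 92 days. The excess over 84 is 5 to 8 days, which is 5/89 = 5.6% to 8/92 = 8.7% of the window.
- Falls before week 0 counted at week 12, per arm: 40 × 5/182 = 1.1 to 40 × 8/182 = 1.8.
- Apparent week-12 rate ratio when the truth is 0.70: (84 × 0.70 + 5)/89 = 0.717 to (84 × 0.70 + 8)/92 = 0.726.
- An exposure offset does not remove this, because the falls belong to the wrong period in both arms.
- At week 24 the extra 5 to 8 days fall within the intervention period. The problem there is possible double counting, and the dilution figure above does not apply.

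**The case against.** The strongest reply is that falls are one of several secondary outcomes, that the objective and the primary outcome concern postural stability, and that the falls comparison will be imprecise whatever is done. That largely stands. For a true ratio of 0.70, |ln 0.70| = 0.357, which is 0.357/0.329 = 1.1 standard errors with complete reporting and 0.357/0.394 = 0.9 after 30% loss. Better recording would not turn this into a powered comparison. It would make the description of falls more complete.

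A second reply is that three months is loose wording for 12 weeks. This is plausible: the falls section ties the window to the 12-week periods, and the Outcomes section calls the 24 weeks 6 months. A gap of more than about a week between randomisation and first training would also remove the reach before randomisation. So it cannot be stated as fact that falls before randomisation will be counted.

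A third reply is that the same recall at all three visits keeps the instrument constant, and that a prompted sheet brings an unblinded therapist into ascertainment and depends on attendance. Both parts are fair, and the fix has to deal with them.

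A reader might infer two stronger points that the document does not support:

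- **Recall biases the comparison between arms.** Participants are not listed as blinded, so differential reporting cannot be excluded. But all arms train actively on the same supervised schedule with the same follow-up calls, and nothing indicates that forgetting would differ.
- **Falls will sit in two conflicting records.** The adverse-event section does not name falls, so a second falls record is conjecture.

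**Conclusion.** The point holds as a weakness of measurement in a secondary outcome, of minor to moderate severity. Three-month recall is the only source described, and shorter, dated recording is available at contacts already planned in every arm.

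The main cost is precision: a standard error up to about 20% larger if 30% of falls are forgotten, and about 5% larger at 10%. The forgetting range is assumed, and the expected count of 55 carries an entry criterion forward and may be too high. The window mismatch is a minor wording issue that moves a ratio of 0.70 to about 0.72 to 0.73 at most, and only on a literal reading. The sample size and the primary outcome are unaffected.

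**What to change.** Give each participant a dated falls sheet to fill in, prompted at the existing sessions in weeks 1 to 12 and at the existing calls in weeks 13 to 24. At week 12 the blinded assessor counts falls dated from randomisation to that visit, and at week 24 those dated since the week-12 visit. The assessor also asks about unrecorded falls.

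Keep the week-0 recall as a baseline descriptor or covariate and compare arms on the post-randomisation counts. Baseline and follow-up would then come from different instruments, so change from week 0 should not be the falls analysis.

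At minimum, word the week-12 and week-24 question as falls since the last assessment visit. This removes the overlap between windows, although at week 12 it still includes any days between the baseline visit and randomisation.

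Reconcile the call frequency between Follow-up after intervention and sections {18b} and {22}, since it sets how often the sheet is prompted in weeks 13 to 24.

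The cost is one paper sheet and a short prompt, with no new visit, staff or participants. The two downsides are prompting by a therapist who knows the allocation and capture that depends on attendance and completed calls. Participant-written entries and the blinded count, with its question about unrecorded falls, limit both.

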#### Inclusion criteria

Adults older than 60 years oldAble to maintain the standing positionAble to walk alone, without others, prosthesis or mobility aidsNormal cognitive functionBe at moderate fall risk which is determined by one fall within the last 6 months and more than 10s of the TUG test [27]Availability: three times a week over 12 weeks

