### Statistical methods

#### Statistical methods for primary and secondary outcomes {20a}

The full analysis set includes all randomised participants who take at least one session of intervention. If follow-up data of primary outcomes are missing, last observation carried forward method and multiple imputation method will be carried out to adjust for the missing data and intention-to-treat analysis was utilised.

The statistical analyses, including calculation of the mean and standard deviation, will be performed using SPSS statistical software (version 20.0 for Windows; SPSS, Inc., Chicago, USA). Descriptive statistics will be used separately for every group and for the total sample. Continuous variables will be presented as means, standard deviation, and 95% confidence intervals. And categorical variables will be expressed percentages and absolute numbers. The normality of distribution for quantitative data will be assessed using the Kolmogorov–Smirnov test. Chi-squared tests or Fisher’s exact tests (categorical variables) and one-way ANOVA or nonparametric tests (continuous variables) will be used respectively to test the demographic differences among the IFM, EFM and control groups.

The average effects (difference between the three groups) for all the variables will be estimated using general linear models of multivariate of analysis for repeated measurements (MANOVA) test, which incorporates the three intervention groups (control * IFM * EFM), time (baseline * post-intervention * follow-up) and group-time interaction. To examine the effect size of the treatment, the partial eta squared will be calculated. Bonferroni’s post hoc test will be applied to identify the differences. Once the significant difference of group-time interaction is detected, the one-way repeated measurements will be performed to determine the difference of effect within each group (pre-intervention, post-intervention and follow-up). Statistical significance will be set at 0.05 for all analyses. Analysis will be carried out by an independent researcher.

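### The secondary falls outcome is tested with pre-entry falls as a time level of a repeated-measures MANOVA, which costs power between arms and lets regression to the mean show up in the within-arm tests

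*Protocol article*

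**What the plan says.** The article's falls section, under secondary outcomes, specifies a self-reported count: "the number of falls in the last 3 months will be recorded by each participant". It is collected three times: "Similarly, the number of falls will be reported by participants at the points of baseline (week 0), post-intervention (week 12) and follow-up (week 24"). Its purpose is to judge treatment, since participants are to "recall the falls in the last three months in order to determine the treatment effect of these intervention".

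The section Statistical methods for primary and secondary outcomes {20a} says that the group effects "for all the variables will be estimated using general linear models of multivariate of analysis for repeated measurements (MANOVA) test". The model has group, time and their interaction, and time has three levels, of which baseline is one. If the interaction is significant, a one-way repeated-measures analysis follows within each group. Nonparametric tests are offered only for demographic comparisons, and no count model is named.

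The inclusion criteria define moderate fall risk as "determined by one fall within the last 6 months" together with a Timed Up and Go time above 10 s.

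The falls section ends with a sentence about a different instrument: "The scores of berg scale will be shown as proportion". No summary measure for falls is given.

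**The concern.** The baseline fall count covers the 3 months before the study, and that window lies inside the 6-month entry window (apart from any gap between screening and baseline). Everyone is enrolled because of a recent fall, so the baseline mean is set largely by the entry rule. Two consequences follow if it is used as an outcome level.

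First, the group-by-time test measures each arm against a noisy, selected starting value. Randomisation has already made the arms comparable, so the falls that carry the treatment information are those after randomisation. Testing change from baseline adds noise, and the 4-df interaction spreads one simple question over several contrasts.

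Second, when people are selected for a recent fall, their later counts tend to drop without any treatment effect. A within-arm test over time cannot tell that drop from benefit.

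Falls are secondary, but the trial presents itself as evidence for fall prevention, so readers will look at this result.

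**Working it through.** **1. The plan's own figure.** The sample-size section gives 98 in total for three groups, α = 0.05, power 0.80 and effect size 0.25. Taking 0.25 as Cohen's f, with 3 groups, 3 times and s = 2, the MANOVA interaction has df1 = 4, df2 = 2(98 − 3) = 190 and λ = N·s·f² = 98 × 2 × 0.0625 = 12.25. The noncentral F gives power 0.8005 at N = 98 and 0.796 at N = 97. So 98 is reproduced, and the test it sizes is the 4-df group-by-time interaction. It was not sized on falls.

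**2. What the entry rule does to the baseline count.** Assumed, not in the documents: a source population with mean μ falls per 3 months and a gamma-Poisson count with heterogeneity variance μ² (dispersion 1). With no treatment effect:

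- Entry read as at least one fall in 6 months: baseline 3-month mean = (1 + 2μ)/2; mean in the next 3 months = 2μ(1 + μ)/(1 + 2μ).
- Entry read as exactly one fall: baseline mean = 0.5; next 3 months = 2μ/(1 + 2μ).

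| μ per 3 months | At least one: baseline → next (drop) | Exactly one: baseline → next (drop) |
|---|---|---|
| 0.10 | 0.60 → 0.18 (69%) | 0.50 → 0.17 (67%) |
| 0.15 | 0.65 → 0.27 (59%) | 0.50 → 0.23 (54%) |
| 0.30 | 0.80 → 0.49 (39%) | 0.50 → 0.375 (25%) |

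The size depends on μ. At μ = 0.5 with exactly one prior fall, the next-period mean is 2(0.5)/(1 + 1) = 0.5, so there is no drop at all.

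**3. Power and within-arm behaviour.** Simulation with 40 per arm (sample-size section), two-sided 0.05, full follow-up, and the IFM fall rate halved while the other two arms are unaffected; 2,500 runs per row. The tests are the planned interaction (Pillai), a 2-df negative binomial likelihood-ratio test on falls in weeks 0–24 without covariates, and one-way ANOVA on the same totals. The last column is the share of runs with a significant interaction in which the unaffected control arm also shows a significant within-arm change over time.

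| Entry; μ; dispersion | Interaction | Negative binomial | ANOVA on totals | Control arm significant within arm |
|---|---|---|---|---|
| ≥1; 0.10; 1 | 6.6% | 30.0% | 26.1% | 82% |
| ≥1; 0.15; 1 | 9.7% | 40.3% | 35.4% | 70% |
| ≥1; 0.30; 1 | 16.0% | 60.0% | 54.4% | 42% |
| ≥1; 0.30; 0 | 10.2% | 51.5% | 49.8% | 67% |
| =1; 0.10; 1 | 7.7% | 28.2% | 24.0% | 74% |
| =1; 0.15; 1 | 9.6% | 37.0% | 31.9% | 49% |
| =1; 0.30; 1 | 16.8% | 52.4% | 46.4% | 20% |
| =1; 0.30; 0 | 13.4% | 52.1% | 50.8% | 37% |

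A further set of 1,500 runs per scenario, which also included dispersion 0.5, widens the ranges slightly, to 7–17% for the interaction and 28–62% for the negative binomial.

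**4. Where the loss arises.** From the interaction test to ANOVA on post-randomisation totals the gain is 16 points (24.0 − 7.7) to 40 points (49.8 − 10.2). From ANOVA to the negative binomial it is 1 point (52.1 − 50.8) to 6 points (52.4 − 46.4).

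**5. No effect in any arm.** The interaction test rejects in 3.6% to 5.6% of runs and the negative binomial in about 4% to 6%. A within-arm test run without the gate would be significant in about 17% to 97% of runs.

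**The case against.** The strongest reply is that the comparison answering the trial's question is between arms, and randomisation protects it. That stands. A reader might infer that regression to the mean produces a false benefit of IFM over control. It does not: the drop is common to all arms, and the interaction test keeps its error rate.

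The within-arm tests are also gated on a significant interaction. For falls that gate would open in only 4% to 6% of trials with no effect, and in 7% to 17% with a halved IFM rate. This limits how often the problem arises, but once the gate is open it does not remove it, as the last column of the table shows.

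A reader might also blame normal theory applied to a sparse count. That is the minor cause: 65% to 85% of participants have no fall at week 12 in the no-effect scenarios, yet ordinary ANOVA on post-randomisation totals performs nearly as well as the count model.

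The closing Berg sentence in the falls section could be read as a plan to show falls as a Berg proportion. It also closes the Berg section itself, and variants appear under foot muscle strength and foot arch function. It is a copying slip.

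Finally, falls are secondary, the trial was not sized on them, and every fall rate used here is assumed. All of that is fair. It limits the weight of the point but does not make the chosen analysis a good one.

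**Conclusion.** The point holds as a weakness in a stated analysis, not as an omission that an analysis plan might fill: the article assigns all variables to this model and names baseline as a time level. For a halved IFM fall rate, the planned test has about 7–17% power where a direct comparison of post-randomisation falls has about 28–62%. Type I error between arms is not affected. After a significant interaction driven by IFM alone, the unaffected control arm would still show a significant within-arm change in about 20% to 82% of cases.

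These figures rest on assumed source rates of 0.10–0.30 falls per 3 months, dispersion 0 to 1, either reading of the entry rule, and complete follow-up. At higher source rates the baseline drop can vanish. The documents do not support a claim of bias between arms, nor a claim that a better analysis would make falls confirmatory: no scenario examined reaches 80% power. The plan should be changed, but the primary outcome does not depend on it.

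**What to change.** - Take falls out of the MANOVA. Compare falls reported for weeks 0–12 and for weeks 12–24 (or 0–24 combined) between arms with a negative binomial model, or a Poisson model with robust errors. Use arm, Berg stratum and baseline fall count as covariates and log observed time as offset. Report rate ratios with 95% confidence intervals.
- Do not use baseline falls as an outcome level, and state that within-arm change in falls will not be read as a treatment effect.
- Replace the misplaced Berg sentence in the falls section with the summary to be shown: fall counts and rates per arm and period.
- State that falls are secondary and that the trial is underpowered for them.

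The cost is a few lines of analysis text and one corrected sentence. No new data are needed.

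More frequent fall questions are not part of this fix. The regular contacts, at training sessions and by telephone, are with the physical therapist, who delivers the training and is described as blinded only for baseline assessment. Collecting falls there would move the outcome from blinded assessors to someone who knows the arm.
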